**(Amended January 17, 2003)**

Paediatric dose (0.25 ml dose volume) of the RTS,S/AS02A candidate malaria vaccine will be administered at each vaccination. Full doses (0.5 ml dose volume) of hepatitis B vaccine (Engerix-B™), the 7-valent pneumococcal conjugate vaccine (Prevnar®) and *Haemophilus influenzae* type b vaccine (Hiberix™) will be given to the control group.

Subjects who cannot be vaccinated on the originally scheduled date due to an acute illness (on the judgement of the investigator or designate) or scheduling conflicts will be vaccinated within 7 days and undergo all study procedures for this visit on the same day as vaccination. In the particular case of any child found to be febrile (axillary temperature   37.5°C), a blood slide will be taken to investigate malaria parasitaemia. Children will be treated as appropriate for their condition and will be followed up until resolution of any symptoms and be vaccinated if their clinical symptoms resolve within 7 days.

Those who cannot be re-vaccinated within 7 days of their scheduled date will continue all study procedures apart from receiving further study vaccinations.

### Safety and reactogenicity assessment during 4-day post-vaccination follow-up

On the day of vaccination, all subjects will remain at the vaccination site after vaccination under the supervision Principal Investigator or other designated staff, who will record any adverse events that should occur, according to SOPs. Each vaccinee will be closely observed for one hour or longer if necessary with appropriate medical treatment readily available in case of a rare anaphylactic reaction following the administration of the vaccine. After the observation period, axillary body temperature will be recorded again and, together with any local and general signs and symptoms that may occur, will be recorded in the CISM clinic form by the investigator. Trained staff, drugs and equipment are available in the event of a child collapsing. Trained field workers, under the supervision of the Principal Investigator, will visit each subject at daily intervals for three subsequent days following each vaccine dose (detailed in CISM SOPs). At each visit, the axillary temperature will be taken and recorded on diary cards together with any solicited adverse events. Analgesics are provided to field workers for the treatment of children with injection site pain. Parents will not routinely be provided with these medications. In the event that the field worker finds any severe general solicited or unsolicited sign or symptom or serious adverse event, the subject will be brought to Manhiça District Hospital or Ilha Josina Health Facility for examination by the Principal Investigator or other designated staff. The corresponding clinical data, including treatment provided, will be documented on diary cards and CISM clinic forms and transcribed onto the CRF. Any SAEs will be reported to the DSMB (through the LSM), GSK Biologicals and MVI (see section 8.5.2). Unresolved AEs will be followed-up by field workers until resolution under the supervision of the Principal Investigator and data will be entered onto the diary cards. Similarly, a child with a fever or history of fever will be referred to Manhiça Hospital or Ilha Josina Health Facility for assessment via the morbidity surveillance system.

Diary cards will be checked and verified by the Principal Investigator before transcription onto CRFs after the 3-day field worker follow-up. The Principal Investigator or Co-investigators will check all records on a daily basis and any recorded general adverse event of intensity grade 3 will be checked by one of the CISM physicians. For this purpose, a field worker will be sent to the parent/guardian of the child and ask the parent/guardian to bring the child to Manhiça Hospital or Ilha Josina Health Facility. If necessary, CISM will arrange transport for this visit. Any local adverse event of intensity grade 3 will be notified to the Principal Investigator or Co-investigators if this event has not resolved or diminished in intensity over the 3-day field worker follow-up.

The Principal Investigator has a primary responsibility for the data transcribed onto the CRFs. The Principal Investigator, together with the field worker supervisor, will perform checks to determine that visits are made as required and findings are correctly recorded (as specified in CISM SOPs ) and this will be documented.

### *DSMB review of safety and reactogenicity data per vaccine dose*

***The DSMB will review the reactogenicity and safety data in a subset of the study population after each vaccination, according to procedures specified in CISM SOPs. Briefly, the DSMB will review the blinded safety and reactogenicity data pertaining to the first week post-vaccination of the first 200 children vaccinated. Following the evaluation of these data, the DSMB will make their recommendation for the administration of the subsequent dose of vaccine to proceed. This review will be repeated after each dose.***
**(Amended January 17, 2003)**

### Morbidity surveillance (all subjects)

Morbidity surveillance has been in place at Manhiça District Hospital since 1996 and a similar system will be put in place in Ilha Josina Health Facility for the purposes of this trial (a detailed review of the level of health care service is given in sections 1.1.6 and 1.1.7). These two health facilities are the source of primary care for this area. The surveillance system will provide a comprehensive recording of all outpatient attendances, the investigational results, diagnosis and management. Prior to the start of the study, all parents/guardians of study children will be educated on the appropriate action they should take if their child becomes unwell at any time during the study period. They will be asked not to medicate their child at home, but to seek medical care at either Manhiça District Hospital or Ilha Josina Health Facility.

Study staff (a nurse, medical agent or field worker), will be available 24 hours per day at both health facilities to receive and identify study participants when they present and to ensure complete investigation and documentation of the attendance. For all children attending outpatients within the age range of the trial, they will ask the carer if the child is in this study and request to see the child’s vaccine study identity card and CISM demographic surveillance system ID card (see section 5.2.1 for details of identity cards). If the identity cards are not available, the identity of the child will be confirmed against details held at the health facilities.

The child will then be referred for evaluation by the medical assistant or medical doctor, who will follow CISM SOPs for the examination, investigation and documentation of each presentation. This information will be recorded on a CISM clinic morbidity surveillance questionnaire. This questionnaire will provide a record of the child’s name and study number, key symptoms and signs, axillary temperature, results of the laboratory tests and imaging examinations available at the time of form completion and the diagnosis, the treatment prescribed and will state whether hospital admission was required.

These forms will be retained by the study personnel in the health facility until they are sent to CISM at the end of each working day. At CISM, the questionnaires will be reviewed by the Principal Investigator or delegate. If it is necessary to notify any of these consultations as a serious adverse event, the Principal Investigator or delegate will review the child as necessary and complete an SAE form to notify the event (as specified in section 8.5).

### Passive case detection of clinical cases of malaria (all subjects)

If a child presenting to Manhiça District Hospital or Ilha Josina Health Facility reports fever within the preceding 24 hours or has a documented fever (defined as axillary temperature  37.5ºC) the same procedure described above (section 5.2.4) will be followed. In addition, blood will be collected for determination of malaria parasites and haematocrit by the CISM laboratory staff. Duplicate blood slides will be taken and labeled with the same unique laboratory ID number, which will also be recorded on the CISM clinic morbidity surveillance questionnaire. Both slides will be taken to the CISM Laboratory and stained with Giemsa. One will be read immediately (within 2 hours) and the result reported to guide diagnosis and management. The second slide will be kept for a later reading, according to CISM SOPs, and will determine parasite density for data analysis. Both slides will be stored at CISM. In addition, blood samples will be taken and stored for parasite genotyping.

Passive case detection of clinical cases of malaria in both cohorts will start from the day of first vaccination (day 0) and will continue until study end (month 21). For the purposes of analysis, data obtained from passive case detection from day 0 onwards will be used for an intention-to-treat analysis for vaccine efficacy while the surveillance period with respect to the primary, secondary and tertiary endpoints will start from 14 days post dose 3 (day 74).

The clinical case definition for malaria currently used at Manhiça District Hospital and Ilha Josina Health Facility is a history of fever within the previous 24 hours or documented fever (temperature  37.5°C) at the time of presentation plus any level of asexual *Plasmodium falciparum* parasitaemia. This will not be changed for the trial and all cases meeting this case definition will receive treatment for malaria.

Axillary temperature measurements will be taken throughout this study. It is widely used in the health care provision system because it does not require sterilization of equipment between use. In addition, rectal temperature measurement is not acceptable in many African cultures. Axillary temperature measurement has long been used in malaria research in Africa: consequently, the disease rates and case definitions on which this trial has been designed have used axillary temperatures. It is therefore appropriate that this method continues to be used in this trial.

### Surveillance for malaria infection (Cohort 2)

Four weeks prior to the start of surveillance for malaria infection (i.e. 2 weeks before the third vaccination), asymptomatic parasitaemia will be cleared in children enrolled into Cohort 2 with amodiaquine-SP (sulfadoxine and pyrimethamine : 25 mg/kg body weight p.o. and 1.25 mg/kg body weight p.o. single dose; amodiaquine: 10 mg/kg body weight p.o. once daily for three days). The prevalence of asymptomatic parasitaemia in the study area is high, therefore all children will receive a drug for clearance of malaria parasites without prior blood sampling to determine parasitaemia. The first dose of amodiaquine-SP will be administered at a field worker visit 2 weeks before the third dose of vaccine (day 46). The absence of parasitaemia will be checked by taking blood for a blood slide at clinic visit 4 (day 60). Any child with any level of parasitaemia at this point will be treated with a second-line treatment for malaria and will not undergo the surveillance period for active detection of infection. All such children will not contribute to the endpoint for vaccine efficacy in Cohort 2.

The surveillance period for malaria infection will begin 14 days after the third dose of vaccine (day 74). Surveillance will continue with the clinic visit on day 90 and then field worker visits every two weeks (one visit every 14 days) for the following 2½ months (six visits) and then monthly for 2 months (two visits at months 7 and 8), and ending with the clinic visit at month 8½. Blood samples will be taken for examination of malaria parasitaemia and parasite genotyping at each visit. The first blood slide examination will be made on the first day of surveillance, i.e. 14 days after the third dose (day 74). At first detection of malaria infection with asexual forms of *P. falciparum* in a child, either by field worker surveillance or on clinical presentation with malaria disease at a health facility,the child will be considered to have met the endpoint for vaccine efficacy in Cohort 2 and no further visits for surveillance of infection will be undertaken. The child will still be under morbidity surveillance and will receive monthly visits by field workers for SAE surveillance and will also take part in cross-sectional surveys at month 8½ and month 21.

For the surveillance period for malaria infection, a field worker visit will consist of visiting the child at home and completing a brief surveillance for infection morbidity questionnaire, which will include the reporting of malaria symptoms and a record of axillary temperature. If the child is well and afebrile, blood will be taken by finger prick and blood will be taken for examination of malaria parasitaemia and parasite genotyping. These blood slides will be stained with Giemsa and read to determine the presence of parasites at Ilha Josina Health Facility. Treatment for children not considered to be clinically ill will be sent by a field worker to all blood-slide positive children within 36 hours of the original blood slide being taken.

In the event that a child is reported as having a history of fever within the preceding 24 hours or has a documented axillary temperature of 37.5°C or greater, no blood slides will be taken by the field worker but transport will be arranged by a project vehicle to Ilha Josina Health Facility. The surveillance for infection morbidity questionnaire will record that the child was transferred to Ilha Josina Health Facility. There the child will be reviewed by a clinician or medical agent or assistant, who will complete the CISM clinic morbidity surveillance questionnaire and the child will be managed according to the procedures detailed above (see section 5.2.5) and a finger blood sample will be taken for determination of parasitaemia and parasite genotyping. If parasitaemia is detected in the blood slides taken on arrival at Ilha Josina Health Facility, the child will be treated as appropriate.

For data analysis purposes related to the study, all slides will be transferred to CISM for parasite density reading and storage.

### Monthly home visits to detect SAEs (all subjects)

Field workers will visit each child once every month for 18 months starting from 60 days after last vaccination (day 120) to maintain contact with the subject and his family and to ensure the complete detection of SAEs. The information will also be used for subjects in Cohort 1 to determine period of residence within the study region and hence the period at risk. Absences of 2 weeks or more in duration will be recorded in multiples of 1 week.

These home visits are not designed to monitor the morbidity in the study population. However, if any child is reported to be unwell at the time of a visit, the field worker will advise the parents/guardians to seek care at either Manhiça District Hospital or Ilha Josina Health Facility. In the event that a child is seriously ill the field worker will inform the Principal Investigator or designate and transport arranged to Manhiça District Hospital or Ilha Josina Health Facility, if judged appropriate by the responsible clinician.

During the field worker visits, the children’s parents/guardians will be asked retrospectively if any SAEs occurred since the last visit and this information will be recorded. Unreported SAEs detected in this way will be investigated and reported by the Principal Investigator or delegate on the corresponding SAE forms (see Section 8.5.2). In the case of a death, supplementary information will be gained using the verbal autopsy technique. This will be conducted according to previously published methods[[30]](#endnote-31) and detailed in the SOPs on file with the investigators.

### Cross sectional surveys (all subjects)

All study children will be reviewed at two surveys (months 8½ and 21) to determine safety, immunogenicity and efficacy endpoints. An additional survey will be performed at day 90 (30 days post-dose 3) to determine safety and immunogenicity endpoints only. Parents/guardians will be asked to bring their child to either Manhiça Hospital or Ilha Josina Health Facility on a given day for each cross-sectional survey.

Observations at cross-sectional surveys at months 8½ and 21 will include axillary temperature, spleen size (classified according to Hackett’s Scale, see section 5.7) and body weight. A history will be taken of bednet usage, which will include use of impregnation with insecticides. At all cross-sectional surveys, all subjects will have blood samples taken for:

- Day 90: haematology (blood count) and biochemistry and anti-CS antibodies (anti-HBs antibodies, parasite genotyping and blood slide examination for malaria parasites, if Cohort 2).
- Month 8½: haematology (haematocrit) and biochemistry, blood slide examination for malaria parasites, ***parasite genotyping*** and anti-CS antibodies (~~parasite genotyping and~~ anti-HBs antibodies if Cohort 2). **(Amended August 13, 2002)**
- Month 21: haematology (haematocrit) and biochemistry, blood slide examination for malaria parasites and anti-CS antibodies (anti-HBs antibodies if Cohort 2).

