| · | | Recording of axillary body temperature and any local or general solicited symptoms experienced at time of field worker visit, and within the previous 24 hours, onto diary cards by field workers, on the 3 subsequent days after vaccination. |
| **Clinic Visit 4: Third vaccination (27 to 37 days after Visit 3)** | | |
| **Day 60: Post vaccination 2** | | |
| · | Verification of photo ID and subject number | |
| · | The investigator must record all non-serious adverse events that occur 1 month (minimum 30 days) post-vaccination 2. | |
| · | Reporting of any Serious Adverse Events (SAEs) which the vaccinee has experienced since the previous vaccine dose. | |
| · | Physical examination: recording of pre-vaccination axillary body temperature . | |
| · | Checking of elimination criteria and contraindications to vaccination. | |
| · | Recording of concomitant medication. | |
| · | Intra-muscular (IM) administration of the third vaccine dose in the deltoid region of the left arm. | |
| · | Each vaccinee will be closely observed for one hour or longer if necessary with appropriate medical treatment readily available in case of a rare anaphylactic reaction following the administration of the vaccine. After the observation period, axillary body temperature will be retaken, and together with local and general signs and symptoms that may occur, will be recorded in the CRF by the investigator. | |
| ***Field worker vaccination follow-up visits 7-9 after third vaccination*** | | |
| ***Days 61, 62 and 63:*** | | |
| · | Recording of concomitant medication. | |
| · | Reporting of any Serious Adverse Events (SAEs) which the vaccinee has experienced since last visit. | |
| · | | Recording of axillary body temperature and any local or general solicited symptoms experienced at time of field worker visit, and within the previous 24 hours, onto diary cards by field workers, on the 3 subsequent days after vaccination. |
| **Clinic Visit 5: Follow-up visit after third vaccination and Cross-sectional Survey (30 to 37 days after Visit 4)** | | |
| **Day 90: Post vaccination 3** | | |
| · | Verification of photo ID and subject number | |
| · | Checking of elimination criteria. | |
| · | Recording of concomitant medication. | |
| · | The investigator must record all non-serious adverse events that occur 1 month (minimum 30 days) post-vaccination 3. | |
| · | Reporting of any Serious Adverse Events (SAEs) which the vaccinee has experienced since the previous vaccine dose. | |

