***Laboratory tests during the study: clinic visit 5 (day 90)***

1-2 ml of blood will be obtained from finger prick samples to provide whole blood and a minimum of 0.5 ml of serum for:

- haematology (blood count [BC], which includes platelets, white blood cells, haematocrit and haemoglobin)
- biochemistry (creatinine, ALT, bilirubin)
- serology (anti-CS antibodies)

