***Safety***

- Occurrence of solicited symptoms after each vaccination over a 4-day follow-up period (day of vaccination and 3 subsequent days).
- Occurrence of unsolicited symptoms after each vaccination over a 30-day follow-up period (day of vaccination and 29 subsequent days).
- Occurrence of serious adverse events from the time of first vaccination (month 0) until 6½months post dose 3 (month 8½).

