### Analysis of safety

All safety and reactogenicity analyses will be performed for the Total Cohort.

The overall percentage of subjects reporting any adverse event after vaccination will be tabulated with exact 95% confidence intervals, by type of adverse event; by severity (any grade, grade 3 only); by relationship (No, Yes, respectively).

The overall percentage of doses for which any adverse event is reported after vaccination will be tabulated with exact 95% confidence intervals, by type of adverse event; by severity (any grade, grade 3 only); by relationship (No, Yes, respectively).

The proportion of subjects with at least one report of unsolicited adverse event, classified by MedRA, reported up to 30 days after vaccination, will be tabulated. The same tabulation will be performed for unsolicited adverse events with relationship to vaccination.

Serious adverse events and discontinuation due to adverse event(s) will be described in detail.

Serum ALT, bilirubin creatinine levels, hematocrit values and body weight that are outside of the reference ranges will be described.

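### White cells, platelets and haemoglobin are measured in all children at screening and day 90, but the safety analysis plans no summary of them and no comparison of laboratory results by arm

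*Supplement*

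**What the plan says.** Section 5.2.9 describes the day-90 visit as a safety and immunogenicity survey: "An additional survey will be performed at day 90 (30 days post-dose 3) to determine safety and immunogenicity endpoints only". It applies to everyone ("At all cross-sectional surveys, all subjects will have blood samples taken for") and the first item is "Day 90: haematology (blood count) and biochemistry and anti-CS antibodies". Sections 5.8.3.1 and 5.8.3.2 define the count identically for both cohorts, at screening and at day 90: "haematology (blood count [BC], which includes platelets, white blood cells, haematocrit and haemoglobin". At months 8½ and 21 only haematocrit is taken, so day 90 is the only scheduled white-cell and platelet measurement after vaccination.

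Section 10.7.3 deals with laboratory safety in one sentence: "Serum ALT, bilirubin creatinine levels, hematocrit values and body weight that are outside of the reference ranges will be described". It mentions neither a comparison by arm nor the screening value.

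The visit itself is a "Follow-up visit after third vaccination and Cross-sectional Survey (30 to 37 days after Visit 4" days-window visit, where Visit 4 is the third dose. The unsolicited-event endpoint in sections 10.3.1 and 10.3.2 is: "Occurrence of unsolicited symptoms after each vaccination over a 30-day follow-up period (day of vaccination and 29 subsequent days". Section 10.7.3 tabulates unsolicited events up to 30 days after vaccination. Section 8.1, and the Visit 5 instructions in sections 5.4 and 5.6, require recording for one month with a minimum of 30 days.

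**The concern.** Safety to month 8½ is a secondary objective in both cohorts. Section 1.1.1 calls AS02A a novel adjuvant, and section 1.2.2.6 relies on 990 recipients to define the reactogenicity profile more precisely than the small phase I studies could. That section also says intercurrent infection is frequent here and that the control group helps to separate vaccine effects from illness. The same reasoning applies to blood counts: individual out-of-range values are hard to interpret without the other arm alongside. The protocol draws the blood and measures the cells in both arms, then specifies no display in which a modest difference in white cells or platelets could be seen.

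**Working it through.** **1. Measured against analysed.**

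| Blood-count item | Screening and day 90, both cohorts (5.8.3) | Named in 10.7.3 |
|---|---|---|
| Haematocrit | yes | yes |
| Haemoglobin | yes | no |
| White cells | yes | no |
| Platelets | yes | no |

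One of four items is carried into the safety analysis. The rest of section 10.7 does not pick up the other three. Section 10.7.2.2.5 does compare haematocrit below 25% between groups, but as an efficacy endpoint, in Cohort 1, at months 8½ and 21.

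**2. Adverse-event window against Visit 5.** Dose 3 is nominally day 60. Visit 5 is 30 to 37 days later: days 90 to 97, eight permitted days.

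- Sections 10.3.1 and 10.3.2 (vaccination day plus 29): the window ends on day 60 + 29 = 89, so 0 of 8 days fall inside.
- Section 10.7.3 (up to 30 days): only day 60 + 30 = 90, the nominal visit day, so 1 of 8.
- Section 8.1 and the Visit 5 instructions (one month, minimum 30 days): day 90 is inside. Days 91 to 97 are unclear, because 30 is a minimum.

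Three wordings give three answers on whether a non-serious laboratory finding at Visit 5 counts.

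**3. Distance from screening.** Screening is 7 to 90 days before dose 1. The permitted visit intervals put Visit 5 at 27 + 27 + 30 = 84 to 37 + 37 + 37 = 111 days after dose 1. The two counts are therefore 84 + 7 = 91 to 111 + 90 = 201 days apart. Screening status is useful for stratifying, but the randomised comparison at day 90 carries the inference.

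**4. What the data could show (illustration).** Planned enrolment per arm is 1564/2 + 416/2 = 782 + 208 = 990. With the protocol's losses of 10% in Cohort 1 and 20% in Cohort 2: 0.9 × 782 + 0.8 × 208 = 703.8 + 166.4 ≈ 870.

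Using n = (1.96 + 0.84)² × [p₁(1 − p₁) + p₂(1 − p₂)] / (p₂ − p₁)², two-sided 5%, 80% power, solved for p₂:

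| Assumed control rate p₁ | Detectable p₂, n = 990 | Detectable p₂, n = 870 |
|---|---|---|
| 1% | 2.69% | 2.84% |
| 2% | 4.17% | 4.35% |
| 5% | 8.1% | 8.3% |
| 10% | 14.1% | 14.4% |

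With no cases in an arm, the one-sided 95% upper bound is about 3/n: 3/990 = 0.30% or 3/870 = 0.34%. The documents give no background rate, so p₁ is assumed. The calculation also counts every child as in range at screening. Restricting to such children would shrink n and raise the detectable rates.

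**The case against.** A reader might infer that a blood-count effect would be reported nowhere. The documents do not support that. Section 8.1 counts laboratory-detected changes as adverse events. Section 8.4 requires clinically significant laboratory abnormalities to be followed until normal or explained. Section 8.5.1 mentions blood dyscrasias without hospitalisation among its examples of important medical events. Serious events are recorded for 19 months after the last dose and described in detail, and serious or grade 3 events go to the DSMB. Haematocrit is described.

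A reader might also infer that the day-90 count lies outside the adverse-event window. That holds only under the endpoint wording. Sections 8.1 and 10.7.3 both admit the nominal visit day, and the first two tabulations in section 10.7.3 state no 30-day limit. What stands is an inconsistency between sections.

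The strongest objection is that laboratory tables belong in the reporting and analysis plan (RAP) promised in sections 6.5.1 and 10, which is not shown and could add these parameters. Nor does section 10.7.3 say that its list is exclusive. This has weight, but it is not a full answer: section 10.7.3 names the parameters itself, and a RAP that follows it would repeat the omission. Adverse-event reporting does not fill the gap either, since it captures individual findings that an investigator judges reportable, not a modest group difference.

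Two smaller points are fair. Haemoglobin largely duplicates haematocrit, so white cells and platelets are the real gap. The exact form of the table is partly a matter of style.

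**Conclusion.** The point holds in a limited form. Three of the four blood-count items measured at the day-90 safety survey have no planned summary, and the laboratory sentence in section 10.7.3 plans no comparison by arm for any item. Clinically important individual abnormalities have reporting routes. A non-serious or subclinical difference in white cells or platelets has none. Separately, the adverse-event window is worded in three ways that treat Visit 5 differently.

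The primary efficacy analysis is unaffected. The loss is a safety comparison on roughly 870 to 990 children per arm. Its sensitivity can only be illustrated, because background rates are assumed and all children are taken as in range at screening. The gap itself does not depend on those figures. It rests on reading the parameters named in section 10.7.3 as the ones to be analysed, and on the unseen RAP not having added the others.

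**What to change.** In section 10.7.3, and in the RAP before unblinding:

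- Add white cells and platelets to the laboratory list, and haemoglobin for completeness.
- For each laboratory parameter, tabulate by arm the number and percentage out of range at day 90, split by screening status (in or out of range), with the between-arm difference and its 95% CI, overall and by cohort. Use the reference ranges that section 5.8.3 says will be set in the site SOP.
- Reconcile the adverse-event window across sections 5.4, 5.6, 8.1, 10.3.1, 10.3.2 and 10.7.3, and state whether a laboratory abnormality first found at Visit 5, 30 to 37 days after dose 3, is counted.

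The cost is some wording and one table. The counts are already scheduled, so no extra blood, visits or children are needed.
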